### Participants

Women with postpartum PPGP will be recruited through a simple (convenience) sampling method from the obstetric outpatient clinics of IUMS. The examiner will confirm the diagnosis with the presence of PPGP, and positive diagnostic tests include the following: ASLR, posterior pelvic pain provocation (also known as P4) test, Patric-Faber test, and Gaenslen’s test [33]. The inclusion criteria of the study are (1) primipara women who experienced natural delivery (one month before); (2) age between 18 and 45 years; (3) self-reported pregnancy-related PPGP; (4) a pain score of at least 40 out of 100 mm on the visual analog scale (VAS) [17]; and (5) a score of higher than 2 out of 5 on a 6-point Likert scale for perceived effort during the ASLR test [34]. The exclusion criteria were as follows: (1) the presence of lower back or pelvic pain before pregnancy; (2) history of any fracture in the pelvis and lower extremities; (3) history of spine, pelvis, and lower extremity surgery; (4) neurological diseases; (5) limb length discrepancy; (6) congenital anomaly in the spine, pelvis, and lower extremities; and (7) using any other conservative treatment for pain relief during the study, such as physiotherapy treatment methods. All eligible participants will provide informed consent and sign the consent form before inclusion in the trial. Participants will be free to withdraw at any time during the study.

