### Sample Size

In total, 84 women with postpartum PPGP will be recruited. The optimal sample size was calculated on the basis of the results of a previous study [32]. The pain intensity for intervention groups was 58.2 (SD 13.93) and 64.4 (SD 13.96) at baseline, respectively [32]. We estimated a sample size of 25 in each study arm, which would yield 60% power (α=.1) and an effect size of 0.44 (Cohen *d*) in accordance with calculations performed using G*power software (Version 3.1, Universität Düsseldorf). We also considered an overall dropout rate of 10% (eg, lost to follow-up). Therefore, we aimed to recruit 84 participants (28 in each study arm).

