### Assignment, Randomization, and Blinding (Masking) Procedures

Once participants are confirmed to be eligible, they will be randomly assigned with equal allocation at a 1:1:1 ratio (one control participant per treatment participant) to one of 3 groups: (A) pelvic (narrower) support (n=28), (B) lumbar (broader) support (n=28), and (C) control group (patient-education leaflet) (n=28). Block randomization will be used, with a block size of 6 to achieve balance in allocating participants to study arms [35]. The assessor will perform randomization with a Random Allocation Software (version 1.0) [36]. The nature of this study will not allow for masking of the assessor after assignment to interventions. Only participants will be masked to group assignment at the point of allocation.

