### Intervention

This study will use 2 orthoses: pelvic (Group A) and lumbar (Group B) support (Teb Darman Co). Both orthoses are made of breathable textile material to comfort the participant. Orthoses can be worn on top of or under daytime clothes. The pelvic support will be an adjustable strap (10-15–cm width) fastened below the anterior superior iliac spine (Figure 2A). The lumbar support consists of a pelvic belt attached to the lumbar corset. Lumbar support has a 25-cm width anteriorly and extends from the xiphoid process to the pelvis. It has a 35-cm width posteriorly and extends down from the lower angle of the scapula to gluteal prominences (Figure 2B). Group C (control) will receive only a patient education leaflet containing advice on strengthening exercises, comfortable positions, and other practical information. Participants will be instructed to incorporate the regular activities into their daily routines and not use pain relief medication or other treatment during the following 5 weeks. Although we do not expect participants to experience any trial-related harm, they will be provided with a direct number to contact should they have any questions or queries and report any symptoms related to interventions or any discomfort experienced while wearing their orthoses.

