### Data Analysis

All data will be saved with identification codes to maintain confidentiality. Every effort will be made to follow up on all subjects by the examiner. All enrolled participants, including those who do not complete treatment, will be included in the analysis on the basis of the intention-to-treat principle. Missing data will be replaced by the mean imputation technique, in which the mean of the observed values will be calculated and reported. Descriptive statistics will present demographic characteristics and outcome measures for each intervention group. Multivariate ANOVA will be used to test between- and within-group differences. Data will be controlled for outliers and checked for the normality and homogeneity assumptions. Post hoc (Bonferroni) tests will be conducted to report pair-wise comparisons. SPSS (version 17.0; SPSS, Inc) will be used for statistical analysis, and statistical significance will be set at a *P* value of <.05.

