### Strengths and Limitations

The strength of this study will be the investigation of the effectiveness of newly designed lumbar support for the management of PPGP. There may be limitations to this study. The inclusion and exclusion criteria set in this study can limit the generalizability of the results. Another limitation could be that some participants may be excluded because of incomplete trial time or not being interested in wearing the support.

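### The article promises an intention-to-treat analysis of all enrolled women, yet foresees exclusions that can arise after randomisation and can depend on arm

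*Protocol article*

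**What the plan says.** Four sections of the protocol article bear on who is analysed.

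- **Data Analysis** sets the analysis population: "All enrolled participants, including those who do not complete treatment, will be included in the analysis on the basis of the intention-to-treat principle". It then adds: "Missing data will be replaced by the mean imputation technique".
- **Participants** lists seven exclusion criteria. The first six concern history or existing conditions. The seventh is "using any other conservative treatment for pain relief during the study, such as physiotherapy treatment methods".
- **Assignment, Randomization, and Blinding** places allocation after the eligibility check: "Once participants are confirmed to be eligible, they will be randomly assigned with equal allocation at a 1:1:1 ratio". It also says that the assessor performs the randomisation and cannot be masked afterwards.
- **Strengths and Limitations** says that "some participants may be excluded because of incomplete trial time or not being interested in wearing the support".

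Two further places give context. The Intervention section tells participants to "not use pain relief medication or other treatment during the following 5 weeks", and says that "Group C (control) will receive only a patient education leaflet". Adverse Events and Dropouts says only that discontinuations and their reasons will be recorded and reported. No section says whether a woman excluded under criterion 7, or for the reasons given in the limitations paragraph, is still followed and analysed.

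**The concern.** An intention-to-treat analysis protects the randomised comparison only if no woman leaves the analysis set because of something that happens after allocation. The article states that principle without qualification, then names reasons for exclusion that can arise after allocation: using another treatment, not completing the trial period, and not wanting to wear the support.

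These reasons need not fall evenly across the arms. Group C has no support, so refusing one after allocation can occur only in A and B. Use of other treatment may depend on how much pain a woman still has. It may be more common in C, where no device is given; that is plausible, but it is an assumption and nothing in the article says it. The person who would apply any exclusion may also know the arm, since the assessor is unmasked.

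At stake are the lumbar-support-versus-control comparison on pain, which is the first aim, and the comparison between the two supports. Outcomes at T2 to T4 that are not collected because a woman was taken out cannot be recovered later.

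**Working it through.** **1. The sections side by side**

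| Question | Data Analysis | Participants, criterion 7 | Strengths and Limitations |
|---|---|---|---|
| Woman does not complete | Kept | Not addressed | May be excluded |
| Woman does not want the support | Kept, if enrolled | Not addressed | May be excluded |
| Woman uses other treatment after allocation | Kept, if enrolled | Meets an exclusion criterion | Not addressed |

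Randomisation follows confirmed eligibility. A woman already in physiotherapy can be caught by criterion 7 at screening. A woman who starts it in week 2 cannot, yet the wording covers her as well. Failure to complete the trial period can arise only after entry.

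**2. The article's own figures**

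The Sample Size section gives means of 58.2 (SD 13.93) and 64.4 (SD 13.96).

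- Difference: 64.4 − 58.2 = 6.2 mm.
- Pooled SD: √((13.93² + 13.96²)/2) = 13.945, so d = 6.2/13.945 = 0.445, in line with the stated 0.44.
- With d = 0.44, one-sided α = 0.1 and 25 per arm, a two-sample t test has power 0.603, so the stated 25 per arm reproduces. (The article does not state sidedness; a two-sided α of 0.1 gives about 0.46.)
- 25/(1 − 0.10) = 27.8, rounded up to 28 per arm, or 84 in all.

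The present point changes none of these figures. They supply only a scale: SD about 14 mm, 28 women per arm, 10% dropout and a 6.2 mm difference.

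**3. How far could exclusions move an arm mean?**

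The number excluded and its link to outcome are assumptions. The base case is 3 of 28 (10.7%), close to the planned 10% dropout, taken from one arm only.

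*(a) Share times difference.* If a share q is excluded and their mean differs from that of the retained women by D, the arm mean shifts by q × D.

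- q = 10%, D = 5 mm: 0.5 mm, or 0.5/6.2 = 8%.
- q = 10%, D = 14 mm (about 1 SD): 1.4 mm, or 23%.

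*(b) Selection on outcome.* If exactly the k worst of 28 normally distributed outcomes are dropped, the shift is SD × (sum of the k largest expected normal order statistics)/(28 − k). For k = 3 the three values are 2.014, 1.581 and 1.327, with sum 4.922. The shift is 14 × 4.922/25 = 2.76 mm. If exclusion is only correlated with outcome at r, multiply by r.

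| Excluded | r = 1 (exactly the worst) | r = 0.5 | r = 0.2 |
|---|---|---|---|
| 3 of 28 | 2.8 mm (44% of 6.2) | 1.4 mm (22%) | 0.55 mm (9%) |
| 6 of 28 | 5.0 mm (81%) | 2.5 mm (40%) | 1.0 mm (16%) |

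At about 10% excluded, the range over both approaches is about 0.5 to 2.8 mm. The second row doubles the planned dropout and is shown only to mark the extreme.

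**The case against.** The strongest reply is that Data Analysis is the only section that defines the analysis population, and that it is explicit. The limitations sentence is a remark in the Discussion and says only that exclusion may happen. It follows a sentence on generalisability, so unwillingness to wear the support could describe women who decline before enrolment, and exclusion could be loose wording for loss to follow-up. Criterion 7 stands in a list of eligibility criteria, and the instruction against other treatment in the Intervention section carries no removal from analysis. Stopping a woman's participation and keeping her in the analysis set can also coexist, since missing values are to be imputed.

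Much of this stands. A reader might infer that the article orders these women to be removed, or that criterion 7 can be met only after randomisation. The text supports neither: the limitations wording is conditional, and ongoing treatment can be detected at screening.

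The reply does not remove the conflict. Failure to complete arises after entry, and non-completers are the very group that Data Analysis promises to keep. Criterion 7 is worded to cover conduct throughout the study. Mean imputation fills gaps, but it does not say whether an excluded woman is in the analysis set or still measured, and it cannot recover her actual outcome. A separate analysis plan might choose among these readings, but the article's statements would still conflict.

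The objection to the size is also fair. The documents give no exclusion rate and no relation to outcome, and the 6.2 mm yardstick is a baseline difference between groups in an earlier study, not a treatment effect.

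**Conclusion.** The point holds as an inconsistency that should be settled before recruitment. The article commits to analysing all enrolled women, and elsewhere allows for exclusions that can follow randomisation and can depend on arm. Acting on them would break the randomised comparison.

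The bias is a risk, not an established result. Its direction is unknown: losing women with poor outcomes flatters whichever arm loses them, and losses in different arms may offset one another. Its illustrated size is about 0.5 to 2.8 mm, or roughly 8% to 44% of 6.2 mm. This assumes 3 of 28 women excluded from one arm, an SD of 14 mm, and a link to outcome ranging from weak to complete.

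Two stronger readings are not supported. A bias of about 80% of the sizing difference would need the six worst of 28 women to be removed from one arm, about twice the planned dropout, with nothing offsetting it. That controls are the likeliest to seek other treatment is conjecture; only the absence of a support to refuse in group C follows from the text. The contradiction itself depends on none of these figures.

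**What to change.** Reconcile Participants, Data Analysis, and Strengths and Limitations, with the intention-to-treat statement in Data Analysis governing.

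1. Word criterion 7 as a condition that is checked before randomisation.
2. After randomisation, record use of other treatment and wearing time as data, not as grounds for exclusion.
3. State that women who use other treatment, stop early or do not wear the support continue to be measured at T2 to T4 wherever they agree, and are analysed in their randomised arm.
4. Delete the exclusion sentence in Strengths and Limitations, or correct it to say that non-completion and non-wearing may occur and will be reported by arm.

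A per-protocol analysis is optional and should be only a sensitivity analysis. Nothing here alters what participants are told about other treatment.

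The cost is protocol wording, two case-report-form fields and the effort of measuring women who have stopped. The sample size calculation is unchanged. The downside is some dilution of the primary estimate by non-adherence.

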### Assignment, Randomization, and Blinding (Masking) Procedures

Once participants are confirmed to be eligible, they will be randomly assigned with equal allocation at a 1:1:1 ratio (one control participant per treatment participant) to one of 3 groups: (A) pelvic (narrower) support (n=28), (B) lumbar (broader) support (n=28), and (C) control group (patient-education leaflet) (n=28). Block randomization will be used, with a block size of 6 to achieve balance in allocating participants to study arms [35]. The assessor will perform randomization with a Random Allocation Software (version 1.0) [36]. The nature of this study will not allow for masking of the assessor after assignment to interventions. Only participants will be masked to group assignment at the point of allocation.

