## Methods

### Study Design

A prospective 3-armed, participant-blinded, randomized controlled trial (interventions versus control group) will be performed to investigate the aims. The Template for Intervention Description and Replication (TIDieR) checklist and related guidelines will be used to report the study process [29,30]. The TIDieR checklist describes a standard way to document details carefully and allows authors to write interventions in their studies clearly [29]. The CONSORT-EHEALTH (Consolidated Standards of Reporting Trials of Electronic and Mobile Health Applications and onLine TeleHealth) checklist will be used to report data efficiently as an eHealth intervention trial [31].

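### The unmasked assessor performs the randomisation in fixed blocks of 6, so allocation as described is not protected, and the participant-blinded label claims more than the design can deliver

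*Protocol article*

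**What the plan says.** All references are to the protocol article.

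- **Who randomises** (Assignment, Randomization, and Blinding): "The assessor will perform randomization with a Random Allocation Software (version 1.0".
- **Assessor masking** (same section): "The nature of this study will not allow for masking of the assessor after assignment to interventions".
- **Blocks and ratio** (same section): "Block randomization will be used, with a block size of 6 to achieve balance in allocating participants to study arms"; "they will be randomly assigned with equal allocation at a 1:1:1 ratio". The section opens by placing confirmation of eligibility before assignment.
- **Participant masking** (same section): "Only participants will be masked to group assignment at the point of allocation".
- **Label** (Study Design): "A prospective 3-armed, participant-blinded, randomized controlled trial (interventions versus control group) will be performed". The Abstract's Methods paragraph uses the same label without qualification.
- **Arms** (Intervention): a pelvic strap 10-15 cm wide; a lumbar support 25 cm wide in front and 35 cm behind; or a leaflet with no device.
- **Primary outcomes** (Primary Outcome Measures): pain on a visual analogue scale and the modified Oswestry Disability Index (ODI), both completed by the participant.
- **Other roles**: the examiner confirms the diagnosis (Participants) and conducts the joint position test (JPR of Hip Abduction). A certified orthotic practitioner is involved in all tests (Outcome Measures).

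**The concern.** There are two separate problems.

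**Control of the sequence.** Randomisation protects the comparison only if nobody who influences entry or measurement can foresee the next assignment. Here it is given to the assessor, read in the usual sense as the person who measures outcomes, who knows every past assignment. One fixed block size makes later assignments in each block partly or wholly predictable even without the list. If that person also decides entry, a borderline judgement on the provocation tests, or the timing of enrolment, could follow the expected arm. Analysis cannot reliably repair selection of this kind. The Abstract's Conclusions also state an expectation that the broader support will do better, so the direction of any steering would not be neutral.

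**The label.** A reader told that participants are blinded will discount expectation effects. Those effects matter most for self-reported pain and disability, which are the two primary outcomes. The first aim in the Introduction, lumbar support against control on pain, is a contrast in which the woman sees whether she has a device. Strengths and Limitations mentions neither the participants' awareness nor the unmasked assessor.

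**Working it through.** **Inputs.** Block size: "Block randomization will be used, with a block size of 6 to achieve balance". Ratio 1:1:1. Total: "we aimed to recruit 84 participants (28 in each study arm".

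**Step 1: the plan's own figures.** 84 / 6 = 14 complete blocks. Each block holds 6 / 3 = 2 assignments per arm, and 14 × 2 = 28 per arm. These figures are coherent.

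**Step 2: possible blocks.** 6! / (2! × 2! × 2!) = 90 equally likely orderings of AABBCC.

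**Step 3: predictability from the block size and past assignments only.** For each position in the block, the table gives the probability that the next assignment is certain, the probability that at least one arm is already used up, and the success rate of the best guess (the arm with most places left).

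| Position | Certain | An arm ruled out | Best guess correct |
|---|---|---|---|
| 1 | 0 | 0 | 1/3 |
| 2 | 0 | 0 | 2/5 |
| 3 | 0 | 1/5 | 1/2 |
| 4 | 0 | 3/5 | 8/15 |
| 5 | 1/5 | 1 | 3/5 |
| 6 | 1 | 1 | 1 |
| Sum per block | 1.2 | 2.8 | 3.367 |
| Share of 6 | 20% | 46.7% | 56.1% |
| × 14 blocks | 16.8 | 39.2 | 47.1 |

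Two entries by hand:

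- Position 5 is certain when the last two places belong to the same arm. Given one of them, 1 of the 5 other places matches, so the probability is 1/5.
- At position 4, the three places left are one per arm with probability 2/5 (best guess 1/3), and otherwise two of one arm and one of another (best guess 2/3). This gives 2/5 × 1/3 + 3/5 × 2/3 = 8/15.

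Pure chance gives 1/3, or 28 of 84.

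**Step 4: with the list.** If the person who generates the sequence also holds it, all 84 assignments are known.

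**Step 5: the label against the arms.**

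| Contrast | Can the participant be masked to treatment? |
|---|---|
| Pelvic support against leaflet | No: she has a device or she does not |
| Lumbar support against leaflet | No, for the same reason |
| Pelvic against lumbar support | Not to the device worn; at most she is unaware of the hypothesis or of the other device |

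The assignment section limits masking to the moment of allocation. T2, T3 and T4 all come after the support has been fitted or the leaflet given.

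**The case against.** A reader might infer that the trial has no concealed allocation, that the whole list is known before women are enrolled, and that selection bias is therefore built in. The documents do not support that.

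- The article does not say that concealment is absent, when the list is produced or who keeps it. Such detail is commonly left to a full protocol, which is not shown.
- Eligibility is confirmed before assignment. This does not establish concealment, but it belongs in a fair account.
- The route to selection bias is strongest if the assessor is also the examiner who confirms eligibility. The Participants and JPR sections suggest this, since the examiner does both diagnosis and an outcome test, but no sentence says so.
- The two scored entry criteria, pain and straight-leg-raise effort, are rated by the woman. The room for examiner judgement is mainly in the provocation tests.

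A reader might also infer that no participant masking of any kind is possible. That too goes further than the text: masking at the moment of allocation is possible, and between the two supports women could be unaware of which is favoured. The assessor's lack of masking is openly disclosed.

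These limits stand, and they narrow the point without removing it. The assessor's role in randomisation and the single block size are stated rules, not gaps, and any safeguard in a fuller document would have to override or qualify them. Not knowing the hypothesis is not blinding to treatment.

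**Conclusion.** The point holds in this form: the stated roles and the fixed block size leave allocation unprotected as described, and the unqualified participant-blinded label is broader than the article's own masking statement and untenable for either support against the leaflet.

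Without the list, 20% of assignments are certain and 56% can be guessed. This assumes a person who knows the block size and sees every past assignment in order. The 100% figure depends on that person holding the list, which is not documented. All of these figures measure predictability; none estimates bias in pain or ODI.

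The participants' awareness bears on both primary outcomes and on the self-rated effort score. The assessor's awareness bears mainly on the force and joint position tests. No sample-size figure is affected.

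**What to change.** 1. Have a person who neither recruits nor measures generate and hold the sequence, and replace the sentence that gives randomisation to the assessor.
2. Use randomly varied block sizes, for example 3 and 6, not disclosed to those who recruit or measure.
3. Reveal each assignment only after eligibility, consent and T1 measurements are complete.
4. In the Abstract and Study Design, replace participant-blinded by open-label. If participants are not told the hypothesis, say only that. Align the sentence in the assignment section.
5. In Strengths and Limitations, state that pain and ODI are unblinded self-reports and that the force and joint position tests are made by an unmasked assessor. If staff allow, a separate masked assessor looks feasible at T4, when the supports have been off for a week.

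**Cost.** A reassigned task, concealment materials and some rewording. The article names no statistician or other independent person, so someone has to be found for the task. Arms may end slightly unequal. With blocks of 3 and 6, stopping at 84 can cut a block of 6 only after three assignments, so the largest difference is two (2, 1 and 0). With blocks of 9 it could reach three. The total stays at 84.
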